**Fig. 1 Fig1:**
[figure not shown]
Flow diagram for study participants

### Study outline

Routine standard preoperative and postoperative clinical care in the participating institutions do not currently include special nutrition, exercise and psychological support to cope with anxiety before surgery. As usual, patients are evaluated in the preoperative clinic before surgery to determine whether they are fit for surgery and to adjust their medication for co-morbid conditions. It is not common practice after surgery to offer them an in-hospital exercise program but patients are given generic instructions by the surgeons about mobilization and returning to normal activities. Some patients may be referred to a physiotherapist by their surgeon. Nutrition, exercise and coping strategies will be introduced solely for research purposes. All patients will be screened four weeks before surgery to capture insufficient hemoglobin levels (thresholds in Canada: > 11.2 g/dl, Europe: > 7 mmol/l). Hemoglobin levels in patients with iron insufficiency will be optimized using iron injections (ferinject).

Perioperative care will be based on a standardized, multi-element, evidence-based, comprehensive, ERAS guideline in line with the consensus review of optimal care for patients undergoing colorectal surgery [27]. The guideline will be applied in all participating centers to improve generalizability.

The diagnostic work-up for patients with a tumor suspected for malignancy at colonoscopy will be finalized within one week while awaiting definitive pathology. An individual treatment strategy will then be proposed by the multidisciplinary team. Patients that meet the criteria for the trial will be scheduled approximately five weeks after the final diagnosis. This schedule allows for the implementation of a four-week prehabilitation program.

The multidisciplinary multimodal prehabilitation program is composed of 4 elements: exercise training, nutritional intervention, smoking cessation and psychological support. The exact interventions are shown in Table 1 and described in detail below:

**Table 1 Tab1:** Prehabilitation interventions

Prehabilitation randomized controlled trial scheme							
	Preoperative			Operation	Postoperative		
Weeks	−5	−4	−1	0	4	8	52
	Before start	Baseline (t0)	Preoperative (t1)	Surgery	30 day follow up (t2)	8 weeks follow up (t3)	1 year follow up (t4)
Gastroenterologist	Inform patient	–	–	–	–	–	–
Casemanager	Inclusion patient	G8 score	–	–	–	–	–
Sport physician	–	Informed consent VO2max Anaerobic threshold Exercise-ECG	VO2max Anaerobic threshold Exercise-ECG	–	VO2max Anaerobic threshold Exercise-ECG	–	–
Physiotherapist	–	6MWT Stair climb test Sit-to-stand test 1-RM Activity questionnaire Fried Frailty Score	6MWT Stair climb test Sit-to-stand test Activity questionnaire	–	6MWT Stair climb test Sit-to-stand test Activity questionnaire	6MWT Stair climb test Sit-to-stand test Activity questionnaire	–
Dietician	Food diary	Height, weight Weight loss %^a^ Anthropometry Hand grip strength PG-SGA	Food diary Height, weight Weight loss %^a^ Anthropometry Hand grip strength PG-SGA	–	Height, weight Weight loss %^a^ Hand grip strength PG-SGA	Height, weight Weight loss %^a^ Wrist/abdominal/ Hand grip strength PG-SGA	–
Psychologist	–	Intake Coping with anxiety^c^	–	–	–	–	–
Anesthesiologist	–	–	Preoperative screening^b^	ERAS^b^	–	–	–
Surgeon	–	–	ERAS**	–	–	–	–
Surgical resident	–	–	–	–	Outpatient data	–	–
Researcher	–	HRQoL GAD-7 PHQ-9	HRQoL GAD-7 PHQ-9	–	30-day morbidity and mortality HRQoL GAD-7 PHQ-9	HRQoL GAD-7 PHQ-9	Mortality HRQoL GAD-7 PHQ-9

^a^weight loss in the past 3–6 months. ^b^Following Enhanced Recovery After Surgery (ERAS) guidelines. ^c^when indicated, as stated in the protocol

#### Exercise program

An exercise specialist (kinesiologist, sport physician) will assess the patients’ mobility and his/her capacity to exercise using a cardiopulmonary exercise test (CPET). The CPET values will be used to establish an individualized dosing of training embedded in a standardized training program [28].The interval training duration is 28–32 min and performed with 4 min of warm-up at moderate intensity, 4 intervals of High intensity (2–3 min) and 4 intervals of Moderate intensity (4 min).The workload is dosed at the wattage corresponding to 90% the peak wattage as attained by the CPET. This is aimed to result in a metabolic response ranging from 85 to 100% of VO2peak during the high intensity intervals. This corresponds with a heart-rate of 85–100% of maximal heart rate, and a Borg score of 15–17. Moderate intensity is set at 30% of peak wattage of the CPET test. This is aimed to have recovery at a level around or just below Aerobic Threshold.If the patient is unable to complete the high-intensity bout for 4 periods of 2 min (=less than 8 min’ exercise in the high intensity range), the intensity is reduced by 10 %. The intensity is reduced further – in steps of 10 % – until the patient can complete the 4 bouts of at least 2 min. If the patient is able to complete all 4 high intensity bouts for 3 min (12 min in the high intensity range) the load is increased with 10%. If necessary fine-tuning can be done using steps of 5%.

In addition to the preoperative exercise program, patients will receive information about breathing techniques to prevent pneumonia.

Patients in the intervention group will have three supervised in-hospital training sessions per week during four weeks. This includes interval training and resistance training.

The interval training duration is 28–32 min and performed with 4 min of warm-up at moderate intensity, 4 intervals of High intensity (2–3 min) and 4 intervals of Moderate intensity (4 min).

The workload is dosed at the wattage corresponding to 90% the peak wattage as attained by the CPET. This is aimed to result in a metabolic response ranging from 85 to 100% of VO2peak during the high intensity intervals. This corresponds with a heart-rate of 85–100% of maximal heart rate, and a Borg score of 15–17 Moderate intensity is set at 30% of peak wattage of the CPET test. This is aimed to have recovery at a level around or just below Aerobic Threshold.

If the patient is unable to complete the high-intensity bout for 4 periods of 2 min (=less than 8 min’ exercise in the high intensity range), the intensity is reduced by 10 %. The intensity is reduced further – in steps of 10 % – until the patient can complete the 4 bouts of at least 2 min. If the patient is able to complete all 4 high intensity bouts for 3 min (12 min in the high intensity range) the load is increased with 10%. If necessary fine-tuning can be done using steps of 5%.

Resistance training is composed as 2 series of 10 repetitions of 6 exercises targeting all major muscle groups).The strength training consists of two series of 10 repetitions of six exercises: leg press, chest press, abdominal crunches floor, lat pull down, low row and step up.○ In week 1 using 65% of calculated 1RM (baseline)○ In week 2 using 70% of calculated 1RM (baseline)○ In week 3 using 65% of calculated 1RM (at 3 weeks).○ In week 4 using 70% of calculated 1RM (at 3 weeks)The 1RM will be determined at baseline and at 3 weeks using. The strength exercises are performed according to: 2 s of concentric strength and 2 s of eccentric strength. The 1RM is calculated by the Brzycki formula:○ *1RM = W*36/(37 –r)**W* = weight in kilograms*r* = repetitionsThe last bout with 10 repetitions needs to be attainable. If this is not the case in the next session dosing will be 5–10% lower. If in the last bout it appears that exercises are to low (≥15 repetitions will be achieved), in the next sessions dosing will be 5–10% higher.

Patients will also be given instructions about how to conduct aerobic exercises at home. Patients are instructed to aim at 60 min walking and/or cycling a day, but at least 30 min a day. If possible, patients can do more than 60 min of walking or cycling every day. In case of a low exercise capacity it is advised to walk/cycle 2–3 times a day for periods of 10–20 min. Also an electric bicycle, a stationary bicycle and/or a walking aid (walker) is allowed if necessary.

Patients in both the intervention and control group will wear an accelerometer for four weeks to count the number of steps walked in order to record the overall activity.

The conventional wisdom is that training blocks of 3–5 min are particularly effective in terms of enhancing exercise capacity. Most of the nine studies that produced the largest increases in VO_2_max (∼0.85/min) used blocks of 3–5 min and HIT. Many of these studies presented either individual data or ranges for VO_2_max values pre- and post-training, and an appraisal of these data suggests that a marked training response was seen in all subjects [29].

In the intervention group we expect to achieve the following improvements after four weeks of prehabilitation compared to baseline measurements: a 10% increase in VO2 peak, a 15% increase in VO2 at anaerobic level, a 20–40% increase in 1-RM tests and an increase of > 20 m in the 6MWT [12, 15, 16, 19, 27].

#### Nutritional assessment and intervention

The nutritionist will complete nutritional assessments at baseline appointments and during the prehabilitation program using the patient-generated subjective global assessment (PG-SGA), body composition (skinfold measurements, mid upper-arm muscle area), hand grip strength and nutritional intake (caloric and protein intake), and a patients’ three-day food diary.

We aim to establish an anabolic condition preoperatively. In cachectic and sarcopenic patients we try to increase lean body mass by 1–2 kg or more during four weeks of prehabilitation. In order to achieve this goal, the target dietary protein intake will be 1.5–1.8 g/kg body weight in all patients [16, 30–35].

Participants will receive high-quality protein supplements containing 30 g of whey protein following exercise and before sleep. Dietary advice will be given in order to achieve adequate oral protein intake spread properly across meals. Since vitamin D is associated with muscle mass and muscle strength [36, 37], vitamin D will be supplemented daily according to guidelines of the Health Council of the Netherlands (10 μg for women aged 50-69y, for men <70y and women <50y with colored skin and/or little sun exposure and 20 μg for women and men aged 70 y or older) [38]. Besides vitamin D, many elderly patients may have other micronutrient deficiencies or ingest vitamins and minerals below recommended doses before and after surgery. Therefore, all other vitamins and minerals are supplied in a multivitamin/mineral supplement containing 50% of the recommended daily allowance.

During the period of hospitalization, the time (in days) that patients consume nil per mouth is recorded. Also, on the day of discharge, a trained dietician performs a 24-h recall questionnaire to estimate oral protein- and energy intake. Nutritional status assessment (PG-SGA) will be performed at 4 and 8 weeks post-surgery by an investigator – trained by a registered dietician.

#### Smoking cessation

A smoking cessation program with intensive counseling and nicotine replacement therapy (NRT) will be offered to all patients during the weeks of prehabilitation. Past and current smoking is measured using questionnaires. Counselling includes group weekly group sessions and telephone calls. NRT may consist of any type of replacement therapy. Approximately 15–20% of our patients are smokers when cancer is diagnosed [13]. The goal is to achieve a smoking cessation rate of 80% before surgery.

#### Psychological coping

It is expected that patients undergoing surgery for cancer are anxious with some component of depression. Since both anxiety and depression can influence the motivation to carry out social and functional activities, psychological strategies can be put in place to help patients to cope with the stress of surgery and disease. Therefore, patients will be screened for anxiety and depression using the GAD-7 and PHQ-9 questionnaires. If these questionnaires result in a high score (GAD-7 of 10 or higher; PHQ-9 score 15 or higher), patients are considered high-risk and will be offered a referral to a psychologist. Referred patients will receive a total of 1.5 h of psychological intervention in the first session and more sessions during the 4 weeks of prehabilitation if necessary.

All patients in the intervention group will be given instructions on relaxation and breathing techniques by a trained investigator. They will be given an instruction CD, which they can use for relaxation techniques at home. After the program, patients will be asked if their perceived usefulness of these techniques. For psychological support, the intervention group will be contacted weekly by the investigator by phone. During these 5–15 min phone calls, a researcher will shortly evaluate personal progression by a standardized set of questions. In order to enhance adherence to the prehabilitation program, all patients in the intervention group will receive an instructional brochure that includes information about all elements of the program.

### Study outcomes

The initial primary outcome will be postoperative complications, as scored by the Comprehensive Complication Index [39], with the relevant data being collected as a continuous variable and calculated using the sum of morbidity and mortality presented on the Clavien Dindo classification [40]. The CCI score will be calculated at the 30 days of follow-up. The second primary outcome will be the 6MWT measured at 4 weeks after surgery and compared to baseline. The 6MWT will additionally be measured directly after prehabilitation and 8 weeks after surgery.

Secondary outcomes will include patient reported outcome measurements (PROMs) such as health related quality of life (HRQoL) (EORTC QLQ-CR29 and EORTC QLQ-C30 and RAND questionnaires) and depression and anxiety scores (GAD-7, PHQ-9 questionnaires), functional capacity (CPET including VO2max, VO2peak, AT, the sit to stand test, stair climb test, hand grip strength and activity questionnaire), nutritional status (3-day food diary, PG-SGA, anthropometry), postoperative complications, length of hospital stay, study compliance, patient satisfaction and a cost-effectiveness analysis. All secondary outcomes are measured at baseline, the week before surgery, 4 and 8 weeks and 1 year post-surgery.

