**Methods/design:**

This international multicenter, prospective, randomized controlled trial will include 714 patients undergoing colorectal surgery for cancer. Patients will be allocated to the intervention group, which will receive 4 weeks of prehabilitation (group 1, prehab), or the control group, which will receive no prehabilitation (group 2, no prehab). Both groups will receive perioperative care in accordance with the enhanced recovery after surgery (ERAS) guidelines. The primary outcomes for measurement will be functional capacity (as assessed using the six-minute walk test (6MWT)) and postoperative status determined with the Comprehensive Complication Index (CCI). Secondary outcomes will include HRQoL, length of hospital stay (LOS) and a cost-effectiveness analysis.

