### Statistical analysis

Baseline characteristics of both groups will be compared to assess the adequacy of the randomization. Data will be analyzed on an intention-to-treat basis. In addition, a per-protocol analysis will be performed. Trial results will be published in a respective journal. Primary and secondary outcomes for the intervention and control groups will be compared.

The primary outcome CCI will be described as the mean plus the standard deviation (SD). Since we expect CCI to be right skewed we will also describe CCI as the median plus interquartile range (IQR) and percentage above 20. To test the hypothesis (H0) that the study arms result in similar CCIs (in other words, prehabilitation does not prevent postoperative complications), we will use the Student’s T-test if data are normally distributed. Mann-Whitney U if data are not normally distributed or statistical methods that take into account the possible zero-inflated nature of the data. The second primary outcome 6MWT is a continuous variable. This data will be stated as means, plus SD, at each time point. To accommodate the repeat measurements for individuals, we will use a generalized linear mixed model to statistically test the hypothesis of both study arms being equal in terms of functional capacity over time.

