All secondary outcomes will be described as means plus SD or median plus IQR, with the data being continuous, and measures for each time point being normally and non-normally distributed respectively. Categorical parameters will be described as number plus percentage per time point. Statistical methods will include t-test and the Mann-Whitney U test for continuous parameters, distributed either normally or not normally respectively, at a single postoperative time-point. Categorical outcomes will be analyzed with Chi-square testing or regression analysis (logistic, ordinal or nominal, depending on the definition of the parameter) for single time points. The size of the sample will be calculated on the basis of the primary aim: the reduction of postoperative complications as determined with the CCI score. With our population variables, the CCI mean is 10.4 (SD 14), and the target reduction is 30%. We use an alpha of 0.05 and power of 0.80 (two-sided test). We expect a dropout rate of 10%. We therefore need 714 patients: 357 in each arm. This gives us sufficient statistical power to demonstrate the expected proportion of difference (55% versus 20%) in the 6MWT between baseline and surgery based on previous studies [14, 27]. Approximately 600 eligible CRC patients undergo surgery in one of the six participating hospitals annually. This implies that we will complete inclusion within two years with the inclusion period being followed by a year of follow-up.

Due to limited clinical data regarding effect size of the primary endpoint – CCI - an interim analysis will be performed. The interim analysis is planned if half of the intended number of subjects have completed the 4 week assessment (i.e. timing of the primary endpoint assessment). The intention of the interim analysis is to terminate the study if there is a statistical significant difference between study arms.

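### Two primary outcomes each get their own test under a single alpha of 0.05 with no rule for combining them; family-wise error could reach about 9.8% if either alone suffices

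*Protocol article*

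**What the plan says.** The Abstract (Methods/design) lists two primaries with the walk test first: "The primary outcomes for measurement will be functional capacity (as assessed using the six-minute walk test (6MWT)) and postoperative status". The second of these is scored by CCI.

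The Study outcomes section ranks them by name. CCI comes first: "The initial primary outcome will be postoperative complications, as scored by the Comprehensive Complication Index". Then: "The second primary outcome will be the 6MWT measured at 4 weeks after surgery and compared to baseline".

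The Statistical analysis section plans a separate test for each. For CCI: "To test the hypothesis (H0) that the study arms result in similar CCIs", by t-test, Mann-Whitney U or a method for zero-inflated data. For 6MWT, a mixed model that allows for repeated measures tests whether the arms are equal across the time points.

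The same section states the error rate once, in the CCI sample-size text: "We use an alpha of 0.05 and power of 0.80 (two-sided test"). The inputs are "the CCI mean is 10.4 (SD 14), and the target reduction is 30" (the last figure is a percentage). That text calls the reduction of complications the primary aim. It then says that the same 714 patients give enough power for 6MWT. The interim paragraph speaks of the primary endpoint in the singular and identifies it as CCI.

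**The concern.** Two outcomes carry the label primary, and each has its own null hypothesis. The article has one alpha and no statement of how the two results combine: either suffices, both are needed, or one is tested only after the other. It is also inconsistent on how many primaries there are: two in the Abstract and Study outcomes, one in the interim paragraph.

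What is at stake is the claim that the trial may make. The Discussion states that the study is not blinded. If CCI is null and 6MWT is significant, nothing in the article prevents a confirmatory claim of benefit on the walk test alone, at an overall error rate above the stated 0.05. Nor is it fixed what such a claim would be about. The 6MWT contrast is week 4 against baseline in Study outcomes, arms over time in the analysis text, and baseline to surgery in the power statement.

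**Working it through.** **Inputs from the Statistical analysis section:** control CCI mean 10.4, SD 14, reduction 30%, two-sided alpha 0.05, power 0.80, dropout 10%, 357 per arm (714 in total), interim at half the subjects. **Not given:** the correlation between the two test statistics (varied below) and the level at which 6MWT is tested (assumed 0.05).

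**1. The article's sample size.**
- Difference: 0.30 × 10.4 = 3.12.
- n per arm = 2(z₀.₉₇₅ + z₀.₈₀)² × SD² / difference² = 2(1.960 + 0.842)² × 14² / 3.12² = 316.1, so 317.
- With dropout: 317 / 0.9 = 352.2, so 353 per arm and 706 in total. The stated 714 is within about 1% of this.
- Evaluable at 357 per arm: 357 × 0.9 = 321. The t-test power for CCI is then 80.5%.

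So 714 is reproduced only with the whole 0.05 on CCI.

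**2. Two primaries, each at 0.05, either sufficient.** Under independence, 1 − 0.95² = 0.0975. With correlation, 1 − P(|Z₁| ≤ 1.96 and |Z₂| ≤ 1.96) from the bivariate normal:

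| Correlation | Family-wise error |
|---|---|
| 0 | 9.75% |
| 0.3 | 9.5% |
| 0.5 | 9.1% |
| 0.7 | 8.35% |
| 0.9 | 7.0% |

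If both had to be significant, the error at the final analysis would be at most 5%.

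**3. The interim look, kept apart.** CCI alone, tested at half and at full information, each time at 0.05, has error 8.31%. Adding 6MWT at the final analysis gives 1 − (1 − 0.0831) × 0.95 = 0.129 under independence, and 11.4% at correlation 0.7.

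**4. What each rule costs at 714 patients (321 evaluable per arm, t-test).**

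| Rule | CCI alpha | CCI power |
|---|---|---|
| Fixed sequence, CCI first | 0.05 | 80.5% |
| Unequal split 0.045 / 0.005 | 0.045 | 79.2% |
| Even split 0.025 / 0.025 | 0.025 | 71.8% |

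To restore 80% power, the even split needs 383 evaluable per arm; 383 / 0.9 = 425.6, so 426 per arm and 852 in total.

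**5. The likely discordant result.** On the article's 55% versus 20%, power for 6MWT at 321 per arm exceeds 99.9%. That figure concerns a proportion between baseline and surgery, not the week-4 primary, so it is only a guide. CCI misses significance in about 19.5% of trials (100 − 80.5) even if its assumed effect is real. On these assumptions, a positive 6MWT with a null CCI is the discordant result to expect, and it is the one for which no rule is given.

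**The case against.** The strongest reply is that this is a journal article. Alpha allocation and an interim boundary are often set in the full protocol or the statistical analysis plan, which are not shown, and the article never says that 6MWT is tested at 0.05. This stands as a caution: a rule may exist elsewhere. It does not dispose of the point, because the article itself fixes the two primaries, their tests, the alpha and N. A later plan could not split alpha evenly without taking CCI power at 714 to about 72%.

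Four stronger readings are tempting, and the document does not support them.

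- A reader might infer that the outcomes have no order at all. CCI is called the initial outcome, the primary aim and the primary endpoint, and N rests on it alone. What is missing is a testing rule. The Abstract's reversed list claims no rank.
- A reader might infer that a significant result on either outcome makes the trial positive. The article states no success rule of either kind.
- A reader might quote 16%, the independence value if both outcomes are tested at both looks (1 − (1 − 0.0831)² = 0.159). The interim is motivated by CCI and 6MWT is not named there, so about 13% is as far as the text goes. Most of the excess over 9.8% belongs to the interim, which is a problem even with one primary.
- A reader might conclude that splitting alpha is wrong here. Only the even split is costly.

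It is also fair that the Background ties complications closely to functional capacity, so independence may not hold. No correlation is given, and the range above covers this.

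**Conclusion.** The point holds in this form: two primaries, two tests, one alpha of 0.05 used in full by the CCI sample size, and no rule on how the results combine. The priority given to CCI in wording is not carried into the testing. Family-wise error is up to about 9.8%, on three assumptions: 6MWT is also tested at 0.05, either outcome suffices, and the two are independent. It is about 9.5% at correlation 0.3 and 8.35% at 0.7, so it stays well above 5% unless the correlation is very high. If both outcomes were required, the excess would disappear. The unadjusted CCI interim would take the figure to about 13% (11.4% at correlation 0.7) and needs its own remedy. The rule decides what the trial may claim, so it has to be fixed before outcome data are seen.

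**What to change.** Turn the existing priority into a fixed sequence. Test CCI first, at two-sided 0.05 overall. Treat 6MWT at week 4 against baseline as confirmatory only if CCI is significant; otherwise report it as an estimate with a confidence interval. Align the Abstract, Study outcomes and Statistical analysis sections to this, including the number of primaries and the 6MWT contrast. If a rule already exists in the full protocol or analysis plan, state it in these places.

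Cost: a sentence or two of text. N stays at 714 and CCI power at about 80%. The interim boundary is a separate change that may take a little of that power, and it should also say at what level 6MWT is tested if the trial stops early.

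The downside is real: there is no confirmatory 6MWT claim when CCI is null, which happens in about one trial in five even under the assumed CCI effect. If the sponsor wants to keep such a claim possible, a small unequal split is acceptable. With 0.045 for CCI and 0.005 for 6MWT, CCI power is 79.2% and the total error is at most 0.045 + 0.005 = 0.05.

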The process of improving the functional capacity of the individual in order to enable them to withstand an incoming stressor has been termed *prehabilitation* [15, 16]. Although some approaches have focused on education to prepare patients for procedures [17], few steps have been taken to systematically enhance functional capacity before surgery. With most studies performing single modal interventions only. To investigate the impact of preoperative exercise on the recovery of functional capacity after colorectal surgery, a few pilot studies have been performed which show promising results [14–16, 18, 19].

Subgroup analysis of the study of Carli et al., showed that patients whose functional exercise capacity improved preoperatively, recovered relatively well in the postoperative period - regardless of the exercise technique [20]. However, one-third of patients deteriorated preoperatively despite the exercise regimen, and these patients were also at greater risk of prolonged recovery after surgery. Poor preoperative physical function (fatigue, malnutrition and physical performance) and the presence of anxiety and depression were also significant confounding predictors of prolonged recovery [21–25]. These results suggest that exercise training alone is not sufficient to attenuate the stress response in all patients and that it is also important to address factors such as nutrition and coping behavior that promote beneficial adaptation to training. Gillis et al. conducted a pilot study that showed that significant changes in postoperative functional exercise capacity can be achieved with a prehabilitation program [26]. However, they did not address the clinically relevant relationship between preoperative functional capacity (an increase of more than 20 m on the six-minute walk test (6MWT)), and the postoperative outcome (comprehensive complication index (CCI) reduction of 30%). If functional capacity can be improved preoperatively, we may expect a reduction in postoperative complications.

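### Neither the hypothesis nor the power statement given for the 6MWT addresses the declared second primary endpoint, the 6MWT at 4 weeks after surgery

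*Protocol article*

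**What the plan says.** All references are to the protocol article.

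- **Endpoint (Study outcomes).** "The second primary outcome will be the 6MWT measured at 4 weeks after surgery and compared to baseline". The other visits are supplementary: "The 6MWT will additionally be measured directly after prehabilitation and 8 weeks after surgery".
- **Scale and hypothesis (Statistical analysis).** "The second primary outcome 6MWT is a continuous variable". The planned analysis is a "generalized linear mixed model to statistically test the hypothesis of both study arms being equal in terms of functional capacity over time". The section names no time point for this test.
- **Power (Statistical analysis).** The sample size is derived from the CCI: mean 10.4, SD 14, a 30% reduction, two-sided alpha 0.05, power 0.80 and 10% dropout, giving 357 per arm. The text then adds that this number gives "sufficient statistical power to demonstrate the expected proportion of difference (55% versus 20%) in the 6MWT between baseline and surgery".
- **Metres.** The only 6MWT change given in metres is preoperative. Background speaks of "preoperative functional capacity (an increase of more than 20 m on the six-minute walk test (6MWT". Exercise program expects "an increase of > 20 m in the 6MWT" within the intervention group after four weeks of prehabilitation. No SD is given for the 6MWT, and no expected difference between arms at week 4.

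**The concern.** One primary outcome carries three targets. The endpoint is a continuous measure at a single postoperative visit. The hypothesis covers the whole time course. The power statement uses a proportion, over a window that closes before the endpoint is measured.

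The distinction matters because the intervention is preoperative training, so its most direct effect on walking distance is expected at the pre-surgery visit. The endpoint asks something else: whether the arms still differ four weeks after surgery. A test of equality across visits can answer the first question and say nothing about the second. The assurance of sufficient power also leaves the reader without any figure for the endpoint that was declared primary.

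**Working it through.** **1. The three descriptions side by side**

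| | Time | Scale |
|---|---|---|
| Endpoint | week 4 after surgery against baseline | continuous |
| Hypothesis | over time, no visit singled out | continuous |
| Power statement | baseline to surgery | proportion |

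No two rows agree on both time and scale.

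**2. The plan's own sample size**

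CCI difference = 0.30 × 10.4 = 3.12. Per arm, n = 2 × (14/3.12)² × (1.960 + 0.842)² = 316.1, rounded up to 317. With 10% dropout, 317/0.9 = 352.2, rounded up to 353, against 357 stated. This reproduces within 3%. Evaluable per arm: 357 × 0.9 = 321.

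**3. The stated 6MWT contrast, 55% versus 20%**

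Mean proportion 0.375. Per arm, n = [1.960 × √(2 × 0.375 × 0.625) + 0.842 × √(0.55 × 0.45 + 0.20 × 0.80)]² / 0.35² = 28.8, so 29 for 80% power (35 with continuity correction). With 321 per arm, power exceeds 0.999. The sentence is arithmetically true, but only for that pre-surgery proportion.

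**4. What a joint test over visits would respond to**

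Assumptions, none from the protocol: four visits, compound symmetry, SD σ of 80 to 100 m, correlation ρ of 0.6 to 0.8, 321 per arm. Let the arms differ by 20 m before surgery and by 0 m at weeks 4 and 8. The arm-by-visit test has 3 degrees of freedom and noncentrality 20² × 0.75 × 321 / [2σ²(1 − ρ)].

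| σ (m) | ρ | Noncentrality | Probability of rejection |
|---|---|---|---|
| 100 | 0.6 | 12.0 | 84% |
| 80 | 0.6 | 18.8 | 97% |
| 100 | 0.8 | 24.1 | 99% |
| 80 | 0.8 | 37.6 | >99% |

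**5. What can be said about week 4**

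Under the same assumptions, the SD of change is σ√(2(1 − ρ)) and the residual SD after baseline adjustment is σ√(1 − ρ²). The detectable difference at 80% power is 2.80 × residual SD × √(2/321), or about 0.22 × residual SD.

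| σ (m) | ρ | SD of change | Residual SD | Power for 20 m, change | Power for 20 m, adjusted | Detectable, adjusted |
|---|---|---|---|---|---|---|
| 100 | 0.6 | 89 m | 80 m | 81% | 89% | 18 m |
| 80 | 0.6 | 72 m | 64 m | 94% | 98% | 14 m |
| 100 | 0.8 | 63 m | 60 m | 98% | 99% | 13 m |
| 80 | 0.8 | 51 m | 48 m | 99.9% | >99.9% | 11 m |

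The 20 m used here is borrowed from the preoperative, within-group figure. The protocol gives no week-4 difference between arms.

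**The case against.** The best defence is that the model is right and the rest is detail. A mixed model suits repeated measurements and can deliver the week-4 contrast. Its fixed effects, baseline handling and primary contrast are commonly left to a statistical analysis plan, which may exist here. Study outcomes already fixes week 4 and treats the other visits as supplementary. Means will be reported at each visit, so a null week-4 result would be visible. Much of this stands: the model should stay, and its missing specification is not the point.

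Two things remain. The one hypothesis that the article does state is not the declared endpoint. And no analysis plan can make a power sentence about a pre-surgery proportion apply to a week-4 mean.

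A reader might also infer more than the text supports:

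- **That the trial is sized on the wrong variable.** It is sized on the CCI, and that calculation reproduces.
- **That the week-4 comparison is underpowered.** Within the assumed range, a 20 m difference has 81% to 99.9% power on change scores and 89% or more with baseline adjustment.
- **That the proportion is a responder rate.** The text does not define it. The preoperative 20 m threshold makes that reading plausible, no more.
- **That a false claim of postoperative benefit is built in.** The text specifies neither a 3-df joint test nor an average that includes baseline. The rejection rates above are power to detect a real difference at another visit. They become misleading only if the overall result is reported as a week-4 effect.

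**Conclusion.** The mismatch is in the text and depends on no outside figure: the declared endpoint, the stated hypothesis and the stated power concern different times, and the power statement also a different scale. This should be fixed, but it does not undermine the design. The consequence for the hypothesis is conditional. If it is tested jointly over visits, a 20 m pre-surgery difference with nothing afterwards would lead to rejection 84% to more than 99% of the time, under the assumed SD, correlation and compound symmetry. The consequence for power is that the near-100% implied by 55% versus 20% says nothing about week 4, where the figure depends on an SD and a difference that the article does not give.

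**What to change.** In Statistical analysis, name the between-arm difference at week 4 from the mixed model as the primary 6MWT test. The model should include visit and arm-by-visit terms, with baseline 6MWT as a covariate or a constrained baseline. Make the pre-surgery and week-8 contrasts secondary.

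In the sample-size text, define the 55% versus 20% proportion and label it as a pre-surgery secondary measure. Add the week-4 difference detectable with 80% power, from a sourced SD and correlation and for the same baseline-adjusted analysis. With 321 per arm this is about 0.22 × the residual SD, or 11 to 18 m under the assumed values. A figure from the unadjusted formula would not match the model.

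The cost is wording only, with no change to sample size, visits or data collection. The one downside is that the stated 6MWT power will look less favourable than the present sentence implies. The change should be made before the planned interim analysis.
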